## Abstract

**Background:**

Psychosocial stress is a major risk factor for adolescent depression and anxiety, impacting neurodevelopment through hypothalamic-pituitary-adrenal axis and oxytocinergic system dysregulation. Stress-related alterations in fronto-limbic resting-state functional connectivity (rsFC) have been linked to depression and anxiety disorders, yet the role of oxytocin in these processes remains unclear. Existing research often excludes comorbid anxiety or focuses on adults, limiting insights into developmental trajectories and stress-related brain changes in youth. This study aims to investigate the association of peripheral oxytocin, cortisol, and α-amylase and fronto-limbic rsFC in response to psychosocial stress in adolescents with depressive disorders, comparing those with and without comorbid anxiety disorders and healthy controls.

**Methods:**

This study will include a total of 90 participants (aged 12–17 years), comprising three groups (*n* = 30 per group): (1) adolescents with Major depressive disorder (MDD), (2) MDD with comorbid anxiety disorder, and (3) healthy controls. After a clinical examination and psychometric assessment, participants undergo Magnetic Resonance Imaging to assess rsFC before and after stress induction. Furthermore, Diffusion Tensor Imaging is conducted. Psychosocial stress is induced using the Montreal Imaging Stress Task, which requires participants to solve arithmetic tasks under time and social pressure. Saliva samples are collected at multiple time points to analyse oxytocin, cortisol and α-amylase levels.

**Discussion:**

This study offers valuable insights into the neurobiological mechanisms of stress in adolescents with depression and comorbid anxiety disorders. By examining the relationship between fronto-limbic rsFC and endocrine responses, the findings may inform the development of more targeted interventions, such as neuromodulation techniques, to improve treatment outcomes for this vulnerable population.

**Trial registration:**

This study is registered with the German Clinical Trials Register the date of registration was 28 August 2023 (registration number DRKS00032507).

## Introduction

### Theoretical background

Chronic or repeated psychosocial stress is a critical risk factor for the development and maintenance of depressive and anxiety disorders in children and adolescents [1]. These disorders often emerge during adolescence and are associated with long-term impairments in quality of life, increased risk of chronicity, and substantial societal costs (e.g., disability-adjusted life years) [2]. The developmental stage marks a key period of vulnerability, characterized by substantial remodelling of both functional and structural brain connectivity [3, 4]. Diffusion Tensor Imaging (DTI) studies highlighted ongoing development of white matter tracts involved in emotion regulation and cognitive control [5] with alterations in fronto-limbic connectivity associated with depressive and anxiety symptoms in youth [6, 7].

Additionally, stress exposure contributes to maladaptive trajectories of neurodevelopment, increasing the risk for depressive and anxiety disorders [8, 9]. Chronic stress has been linked to dysregulation of key stress-responsive systems, particularly the hypothalamic-pituitary-adrenal (HPA) axis [10] and the oxytocinergic system [11, 12], both critical for emotion regulation and social functioning [13, 14]. While gonadal hormones have been studied in relation to sex differences in adolescent brain maturation and depressive and anxiety disorders [15], the influence of neuropeptides like oxytocin (OXT) in stress-related neurodevelopmental alterations remains underexplored. Recent work by Bernhard et al. [16] underscores the complexity of the adolescent psychoneuroendocrine stress response in major depressive disorder (MDD), showing altered stress reactivity, including OXT pathways, in this population. These findings complement the broader understanding of how neuroendocrine dysregulation, including OXT and cortisol (CORT), may underlie vulnerability to depressive and anxiety disorders in adolescence [17] .

Neuroendocrine responses to acute stress influence large-scale brain networks [18], yet their effects on fronto-limbic resting-state functional connectivity (rsFC) in adolescents with depressive and anxiety disorders remain poorly understood. The fronto-limbic network—encompassing the amygdala, prefrontal cortex, and anterior cingulate cortex (ACC)—is central to stress adaptation and emotion regulation [19, 20]. Aberrant rsFC within this network has been linked to depressive and anxiety disorders, often reflecting hyperconnectivity in stress-sensitive regions and diminished top-down regulatory control [21, 22]. While studies have linked fronto-limbic rsFC to psychiatric symptoms, many have relied on cross-sectional designs or focused on adults [21], limiting insights into developmental trajectories and stress-related brain changes in youth. Moreover, comorbid anxiety is frequently excluded or assessed only dimensionally, constraining the ability to distinguish between depression alone and depression with comorbid anxiety [21]. Given the high rates of comorbidity [23] and the distinct clinical profiles of these subgroups, a more nuanced approach is necessary to understand how acute psychosocial stress affects fronto-limbic connectivity in adolescent populations.

Beyond connectivity patterns, the neuropeptide OXT has emerged as a potential modulator of fronto-limbic interactions, given its role in social cognition and affect modulation [24]. Peripheral OXT levels have been linked to individual differences in stress responsivity and social withdrawal, both common in youth with depressive and anxiety disorders [25]. While intranasal OXT has been shown to modulate rsFC within emotion regulation networks in healthy adults [26], it remains unknown whether endogenous, stress-induced OXT release similarly affects fronto-limbic rsFC. Furthermore, studies examining OXT’s role in stress-related connectivity changes have yielded inconsistent findings, likely due to differences in sampling methods (e.g., plasma vs. saliva), timing of measurements, and potential confounds like medication use [12].

In parallel, CORT—the end product of HPA axis activation—has been widely studied as a biomarker of stress-related psychopathology [27]. Evidence on OXT-CORT interactions is mixed: some human studies suggest that OXT buffers CORT reactivity [28, 29], while others report that higher stress-induced OXT is associated with increased CORT release and faster recovery [30]. Dysregulated post-stress CORT secretion, often observed in individuals with depressive and anxiety disorders [16, 31], has been associated with altered rsFC [32], particularly in circuits involved in emotional processing and self-regulation [33, 34]. In addition to CORT and OXT, salivary α-amylase (sAA), a marker of sympathetic nervous system activity [35], should be assessed simultaneously [36]. Altered sAA rhythms and reactivity have been observed in adolescents with depression and anxiety [37, 38], underscoring its relevance for understanding neuroendocrine dysregulation in these conditions.

However, little is known about how CORT interacts with OXT and sAA in shaping stress-induced rsFC changes. To our knowledge, no study has examined whether individual differences in OXT, CORT, and sAA reactivity predict fronto-limbic rsFC alterations following acute stress in adolescents with anxiety and depressive disorders.

### Study aim

This study aims to examine associations between peripheral OXT, sAA, and CORT release, and fronto-limbic rsFC in response to psychosocial stress in adolescents with depressive and anxiety disorders, compared to healthy controls. By explicitly comparing adolescents with depression alone, comorbid anxiety, and healthy controls, this research seeks to clarify neurobiological mechanisms underlying depressive and anxiety disorders during a critical period of neurodevelopment.

### Hypotheses

We expect blunted CORT and OXT stress responses in adolescents with MDD (with or without comorbid anxiety) relative to healthy controls, whereas baseline levels of these hormones are not expected to differ systematically across groups. For rsFC, we hypothesize time (pre- vs. post-stress) × group (MDD, COM, HC) interactions within fronto-limbic circuits, with greater alterations in adolescents with depressive disorders compared to healthy controls. Exploratorily, we expect that youth with MDD and comorbid anxiety will show more pronounced endocrine blunting and stronger fronto-limbic rsFC alterations than those with MDD alone. Finally, we hypothesize that stress-induced fronto-limbic rsFC changes will be significantly associated with endocrine reactivity (CORT, OXT, sAA), reflecting shared neuroendocrine mechanisms of stress adaptation.

## Methods

### Study design

This single-centre experimental study includes two experimental groups—adolescents diagnosed with depressive disorder and those with comorbid depressive and anxiety disorders—based on Diagnostic and Statistical Manual of Mental Disorders-IV (DSM-IV) and International Statistical Classification of Diseases and Related Health Problems-10 (ICD-10) criteria. Both groups are compared to a matched healthy control group. All participants undergo the same study procedure.

### Sample size and power analysis

An a-priori power analysis was carried out with G*Power 3.1 [39]. We modelled a one-way fixed-effects Analysis of Variance (ANOVA) with three independent groups (healthy controls [HC], major depressive disorder [MDD], and MDD with comorbid anxiety [COM]).

Previous rsFC studies in adolescents with MDD report medium to large effect sizes. Connolly et al. [40] demonstrated reduced amygdala–prefrontal rsFC in adolescents with MDD compared to controls (medium effect; *d* ≈ 0.4–0.6), although numerical effect sizes were not directly reported. Cullen et al. [41] reported group differences in amygdala–prefrontal connectivity that, when derived from published means and standard deviations, correspond to large effects (*d* ≈ 1.0–1.3).

Assuming α = 0.05 (two-tailed) and a desired power of 1-*β* = 0.80, the analysis indicated a required total sample size of *N* = 84 (28 per group). To account for potential data loss due to head motion or dropout, we plan to include *N* = 90 participants, i.e. 30 per group.

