#### Primary outcomes

The first primary outcome is rsFC. We hypothesize that time (pre- vs. post-stress) × group (MDD, COM, HC) interactions will be observed in fronto-limbic connectivity.

Six a priori fronto-limbic ROIs will be examined: bilateral amygdala, hippocampus, ACC, insula, dorsolateral prefrontal cortex (dlPFC), and ventromedial prefrontal cortex (vmPFC), defined using the Harvard–Oxford cortical and subcortical atlases as implemented in the CONN toolbox [89]. This yields 15 possible pairwise connections. For each subject, mean time series will be extracted from each ROI, pairwise Pearson correlations will be computed, and coefficients will be Fisher’s z-transformed to normalize distributions. Group differences will be assessed using general linear models (GLMs) with time (pre- vs. post-stress) as within-subject factor and group (MDD, COM, HC) as between-subject factor. Sex assigned at birth, age, pubertal status (linear and quadratic terms), and medication status (yes/no) will be included as covariates. Additional psychiatric comorbidities (e.g., ADHD, OCD, PTSD, eating disorders) will be recorded but not included as routine covariates due to diagnostic heterogeneity and low subgroup frequencies; however, planned sensitivity analyses will be conducted excluding participants with additional comorbid diagnoses to assess robustness of findings. Due to the expected small number of left-handed participants, groups will not be matched on handedness; however, EHI scores will be considered as covariates in rsFC analyses. False Discovery Rate (FDR) correction across the 15 tested edges will be applied.

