### Strengths and limitations

A key strength of this study is its multimodal design, integrating fMRI, DTI, and endocrine biomarker analysis to provide a comprehensive view of brain structure and function in response to stress. By including adolescents with comorbid anxiety disorders, a group often overlooked in neuroimaging studies, the project enhances ecological validity and clinical relevance. The sample is well-characterized: clinical diagnoses are made by experts and confirmed with structured interviews, while healthy controls are screened for psychiatric conditions. Further, potential confounders like age, school type, pubertal status, and handedness are controlled to ensure comparability across groups.

Several limitations also must be acknowledged. The clinical sample is heterogeneous in terms of comorbidities, medication use, and therapy status, which may introduce variability in stress responses. Within the comorbid anxiety disorder group, diagnostic heterogeneity is also present, as anxiety disorders comprise distinct conditions (e.g., panic disorder, generalized anxiety disorder) that may differ in genetic contributions and neural activation patterns. Due to recruitment and sample size constraints, subgroup analyses by anxiety disorder type will not be performed. While this approach reflects clinical reality, it may also introduce variability unrelated to our primary research question. Such diversity reflects real-world populations but could obscure more subtle effects. The relatively large sample size (*N* = 90) helps offset this limitation by increasing statistical power. Ongoing therapy in some participants may influence stress responses through learned coping mechanisms; however, given the short timeframe, these effects are unlikely to significantly alter rsFC findings. Additionally, the cross-sectional design forbids causal inferences, underscoring the need for longitudinal research to track changes in connectivity and endocrine function over time or in response to treatment. Finally, while this study focuses on neurobiological and hormonal mechanisms, it remains unclear whether the most effective interventions should target these systems, psychological processes, or both—an important question for future research.

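### The stated 80% power at N = 84 applies to one uncorrected three-group ANOVA with an unstated effect size; it is not shown for the primary time × group test on 15 FDR-corrected edges

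*Protocol article*

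**What the plan says.** Protocol article, Sample size and power analysis: "We modelled a one-way fixed-effects Analysis of Variance (ANOVA) with three independent groups". The inputs are α = 0.05 and "a desired power of 1-*β* = 0.80". The result is N = 84, 28 per group. Two earlier studies of adolescents with MDD are cited in support. The first is described as "medium effect; *d* ≈ 0.4–0.6), although numerical effect sizes were not directly reported"; the second is put at d of about 1.0–1.3. Both concern connectivity differences between groups, not differences in change under stress. The value of f entered in the calculation is not given. The size is then raised: "To account for potential data loss due to head motion or dropout, we plan to include" 90, that is 30 per group.

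Primary outcomes: "We hypothesize that time (pre- vs. post-stress) × group (MDD, COM, HC) interactions will be observed in fronto-limbic connectivity". Six regions give 15 pairwise connections. Each is modelled with time (two levels) within subjects and group (three levels) between subjects, plus covariates. "False Discovery Rate (FDR) correction across the 15 tested edges will be applied".

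**The concern.** The sample size section and the primary analysis describe two different tests. The first is a single between-group comparison at α = 0.05. The second is a family of 15 interaction tests under FDR control. Nothing in the article links the 84 to the second, and neither the effect size on the change scale nor the multiplicity enters the calculation.

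The 80% figure is the only quantitative justification of the sample size. Someone reading the later results will take it as the chance that the primary connectivity analysis finds a true effect. If that chance differs materially, a result with no significant edge would be judged against the wrong yardstick.

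**Working it through.** **Method.** Noncentral F for a one-way fixed-effects ANOVA with three groups: df = (2, N − 3), noncentrality λ = f²N. Covariates are ignored.

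**1. Reproducing N = 84.** Since f is not stated, it has to be back-solved.
- f = 0.35: λ = 0.1225 × 84 = 10.29, power 0.812, and 84 is the smallest balanced N that reaches 0.80.
- Power is 0.80 at N = 84 when f = 0.345. Values of f from 0.345 to about 0.352 all return 84.

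**2. What that f means as d.** The conversion depends on the pattern of means:
- f = d/2: d = 2 × 0.35 = 0.70
- both patient groups shifted equally from controls, f = d√2/3: d = 3 × 0.345/√2 = 0.73
- evenly spaced groups, f = d/√6: d = 0.345 × √6 = 0.85

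All three values lie above 0.4–0.6 and below 1.0–1.3.

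**3. Power at N = 84 over both cited ranges** (both patient groups shifted equally; d in units of the SD of the tested quantity). The last column uses 0.05/15 = 0.0033, the level that the smallest p-value must meet if it is the only one rejected under Benjamini-Hochberg.

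| d | f | one test, α = 0.05 | α = 0.05/15 |
|---|---|---|---|
| 0.4 | 0.189 | 31% | 7% |
| 0.5 | 0.236 | 46% | 13.5% |
| 0.6 | 0.283 | 62% | 24% |
| 1.0 | 0.471 | 97% | 82% |
| 1.3 | 0.613 | >99% | 98% |

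**4. FDR over 15 edges, if f = 0.35 carries over to change scores.** Assumptions: Benjamini-Hochberg at 0.05 (the article says only FDR), controls differing from both patient groups, edges independent or correlated at 0.3, 4,000 simulated trials per setting, N = 84.

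| True edges | Power per true edge | Power for at least one true edge |
|---|---|---|
| 1 | 44–46% | 44–46% |
| 3 | 54–56% | 78–86% |
| 5 | 60–62% | 89–96% |
| 15 | 76–78% | 99–100% |

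With all 90 analysable, power per true edge is 50% with one true edge and 81–82% with all 15.

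**5. The change scale.** With two time points, the time × group F test is a one-way ANOVA on pre-to-post change. The SD of change is σ√(2(1 − ρ)), where ρ is the pre-post correlation. If the group difference in change equals the cross-sectional difference in size, f on change is 0.35/√(2(1 − ρ)). The article gives no ρ; 0.3–0.7 is assumed here.

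| ρ | f on change | one test, α = 0.05 | α = 0.05/15 |
|---|---|---|---|
| 0.3 | 0.296 | 66% | 28% |
| 0.5 | 0.350 | 81% | 45% |
| 0.7 | 0.452 | 96% | 78% |

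If the difference in change is half as large, uncorrected power is 20%, 27% and 43%. Moving to change can therefore raise or lower power.

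**6. Data loss.** The margin is 90 − 84 = 6, or 6/90 = 6.7%. The article gives no loss rate. At an assumed 10% or 20% loss (81 or 72 analysable), uncorrected power at f = 0.345 is 78% or 73%.

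**The case against.** Four points on the other side deserve weight.

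First, a reader might infer that the one-way ANOVA is the wrong model. It is not. With two time points the interaction test has that form and, covariates aside, the same degrees of freedom. What remains is the scale of the effect size and the missing allowance for 15 tests. This point stands.

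Second, a reader might infer that the study has well under 80% power for the effects it cites. That fails for one of the two cited ranges. At d = 1.0–1.3, power at N = 84 is at least 97% uncorrected and 82–98% even at 0.05/15. It is true only of d = 0.4–0.6. This point also stands, and any replacement text must show both ranges.

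Third, the figure of about 45% is the case of a single affected edge. The Hypotheses section expects interactions, in the plural, within fronto-limbic circuits. With three or more affected edges, the chance of finding at least one is about 78% or higher at f = 0.35. This stands as a reason to report several scenarios. It does not rescue the stated 80%, because the article does not define power as at least one edge.

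Fourth, an article may leave f to the full protocol. That would explain the missing number. It would not explain why the stated power belongs to one uncorrected test while the same article specifies 15 corrected ones.

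**Conclusion.** The 80% at N = 84 is a property of one uncorrected three-group ANOVA at f of about 0.345–0.35. It is not shown for the primary connectivity analysis. If f = 0.35 holds on change scores, power per true edge at N = 84 was below 80% in every scenario run, from about 44% with one true edge to 78% with all 15.

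The stronger statement, that the study does not have 80% power or that 90 is too few, is not supported. The article gives no f, no pre-post correlation, no number of affected edges and no definition of power over the 15 tests. Large effects, a high correlation, or several affected edges under an at-least-one-edge definition could each bring power to 80% or more. The conclusion rests on the assumptions stated in the check: Benjamini-Hochberg as the FDR procedure, the chosen pattern of group means, edge correlation of 0 or 0.3, and no covariate adjustment.

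**What to change.** Keep N = 90 and rewrite the power statement.

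- State the f used and the pattern of group means behind it.
- Say that 80% at N = 84 refers to a single uncorrected test.
- Define the powered quantity as the group difference in pre-to-post change, with an assumed pre-post correlation and a range such as 0.3–0.7.
- Replace the 80% claim with FDR-adjusted power for several numbers of true edges, saying whether it is per edge or for at least one edge.
- Show power for both cited ranges. With both patient groups shifted equally at N = 84, it is 31–62% for d = 0.4–0.6 and 97% to above 99% for d = 1.0–1.3 uncorrected, and 7–24% and 82–98% at 0.05/15.
- Optionally add power at 10–20% data loss, labelled as an assumption.

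The remark under Strengths and limitations that the sample size "helps offset this limitation by increasing statistical power" does not invoke the 80%. Softening it is an editorial choice and not part of this correction.

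The cost is a short recalculation and a few sentences. No participants, visits or analyses change; the only downside is that the stated figure becomes less favourable.

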### Eligibility criteria

Eligibility is initially assessed via telephone screening and confirmed at the first study appointment. Participants must be adolescents aged 12–17 years. For the clinical groups, inclusion requires a primary diagnosis of at least moderate depression; the comorbid group additionally requires an anxiety disorder diagnosis. In case of discrepancy between clinical diagnoses and the results according to the structured clinical interview M.I.N.I.-KID, final group assignment is determined through expert consensus. Psychotropic medication and hormonal contraceptives are noted and will be corrected for but are not exclusion criteria. Full inclusion and exclusion criteria are listed in Table 1.

**Table 1 Tab1:** Inclusion and exclusion criteria

**Inclusion Criteria**	**General:** • Adolescents aged 12–17 years • Sufficient understanding of the German language • Written informed consent from participant and legal guardian
	**Depressive Group**: Primary diagnosis of depressive disorders: • Moderate depressive episode (F32.1) • Severe depressive episode without psychotic symptoms (F32.2) • Severe depressive episode with psychotic symptoms (F32.3) • Major depressive disorder, recurrent, moderate (F33.1) • Major depressive disorder, recurrent, severe without psychotic symptoms (F33.2) • Depressive disorder, recurrent, severe with psychotic symptoms (F33.3)
	**Comorbid Group**: Primary diagnosis of depressive disorders and an additional anxiety disorder: • Agoraphobia with/without panic disorder (F40.00/F40.01) • Social phobia (F40.1) • Panic disorder (F41.0) • Generalized anxiety disorder (F41.1) • Separation anxiety disorder of childhood (F93.0) • Social anxiety disorder of childhood (F93.2) • Generalized anxiety disorder of childhood (F93.80)
	**Control Group**: Matched by sex and age; school type, handedness, pubertal status, contraceptive intake are controlled for
**Exclusion Criteria**	**General**: • Pregnancy/lactation • Pubertas praecox vera • Acute suicidal behavior • Glucocorticoid-containing medication • Genetic syndromes • Traumatic brain injury • Endocrinological or immune disorders • Chronic neurological disorders affecting brain development and physiology
	**Cognitive/Developmental**: • Intellectual impairment (IQ < 80) • Attendance at a school for special needs
	**MRI-Specific**: • Metallic foreign bodies (e.g., braces, cochlear implants, non-removable piercings) • Upper-body tattoos • Claustrophobia
	**Psychiatric Disorders**: Current/past diagnosis of: • Psychotic disorders • Autism • Bipolar disorder • Mental and behavioural disorders due to psychoactive substance use • Anorexia nervosa (if BMI < 16,5)
	**Control Group-Specific**: • Current or past psychiatric disorders • In-/outpatient psychiatric or psychotherapeutic treatment

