### Measurements

#### Psychological measures

All participants undergo the M.I.N.I. KID 6.0 [43], a structured clinical interview assessing DSM-IV and ICD-10 psychiatric disorders, to identify comorbid psychiatric disorders in the clinical groups or to confirm the absence of psychiatric diagnoses in healthy controls. Given evidence that childhood adversity can influence CORT responses to acute social stressors [44], retrospective assessment of maltreatment is conducted using the Childhood Trauma Questionnaire – Short Form (CTQ-SF) [45, 46]. The CTQ-SF is a validated 28-item measure covering sexual, emotional and physical abuse, and emotional and physical neglect. Items are rated on a five-point Likert scale (1 = “Never true”; 5 = “Very often true”). A recent meta-analysis supports its structural and construct validity [47].

Attachment anxiety and avoidance are measured with the German short version of the Experiences in Close Relationships Scale-Revised Child version (ECR-RC) [48, 49]. This self-report questionnaire includes 12 statements referring to participants’ relationship with their mother; six measuring attachment avoidance and six assessing attachment anxiety. Responses are rated on a seven-point Likert scale (1 = “strongly disagree”; 7 = “strongly agree”), with lower scores indicating higher attachment security. The ECR-RC has demonstrated excellent validity and reliability in youth samples [48]. Given that attachment patterns influence stress reactivity and OXT may modulate this relationship [50, 51], the ECR-RC was included to assess individual attachment differences in the context of OXT’s effects on stress.

Given the influence of handedness on lateralization [52], handedness is assessed using the Edinburgh Handedness Inventory (EHI; [53]). The inventory includes ten items assessing hand preference for specific tasks (e.g., drawing, eating with a spoon), from which a lateralization quotient (LQ) is calculated. Positive LQ values indicate right-handedness, while negative values reflect left-handedness.

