#### Secondary outcomes

Structural MRI measures will be derived from T1- and T2-weighted images to calculate cortical thickness, surface area, and subcortical volumes. Group comparisons will be conducted using ANCOVAs, controlling for sex, age, and pubertal status, with FDR correction applied across regions.

DTI data will be preprocessed with QSIPrep [98] for denoising, motion and distortion correction, followed by whole-brain tractography and structural connectome reconstruction as outlined in recent protocols [99]. Cortical parcellation will be based on the Brainnetome atlas, and structural connectivity matrices will be derived from streamline counts and weighted by fractional anisotropy. Graph-theoretical measures (e.g., node strength) will be extracted using the Brain Connectivity Toolbox. Between-group differences will be tested using ANCOVAs including sex, age or pubertal status, and medication status (yes/no) as covariates.

Task-based fMRI will be analysed using GLMs to assess BOLD activation during the stress induction task. At the first level, subject-specific GLMs will be estimated, and at the second level, group differences will be examined using ANOVAs. The primary contrast will compare stress versus baseline, with sex, age or pubertal status, and medication status (yes/no) included as covariates.

Exploratory analyses will include depressive and anxiety symptomatology scores as covariates in rsFC, sMRI, and hormonal models to test whether associations remain robust after accounting for clinical variation. Sex assigned at birth will be recorded, and exploratory analyses will examine group × sex interactions. When appropriate, non-parametric tests (e.g., Mann–Whitney U-tests) will be applied in case of non-normal distributions. Relationships between VAS ratings and hormone levels (OXT, CORT, sAA) will be assessed using bivariate correlations. Multiple regression models will also be applied to assess associations between hormonal systems. In the first model, CORT increase will be the dependent variable, with OXT increase, baseline CORT, and group as predictors. In the second model, CORT recovery will be the dependent variable, with OXT and CORT increase as predictors.

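### Handedness is described as controlled across groups, but the structural MRI, DTI and task-fMRI models neither match on it nor adjust for it

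*Protocol article*

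**What the plan says.** Two places in the protocol article claim control of handedness. Table 1 (Eligibility criteria), in the control-group row, names sex and age as the matching variables and then says that "school type, handedness, pubertal status, contraceptive intake are controlled for". The Strengths and limitations section says that "potential confounders like age, school type, pubertal status, and handedness are controlled to ensure comparability across groups".

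The reason for measuring it is given under Psychological measures: "Given the influence of handedness on lateralization [52], handedness is assessed using the Edinburgh Handedness Inventory".

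Handedness enters the analysis in one place, Primary outcomes: "groups will not be matched on handedness; however, EHI scores will be considered as covariates in rsFC analyses". The firm covariate list in the same paragraph does not contain it: "Sex assigned at birth, age, pubertal status (linear and quadratic terms), and medication status (yes/no) will be included as covariates".

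Under Secondary outcomes, each group model has its own stated covariates:
- Structural MRI: sex, age and pubertal status.
- DTI: "Between-group differences will be tested using ANCOVAs including sex, age or pubertal status, and medication status (yes/no) as covariates".
- Task-fMRI: sex, age or pubertal status, and medication status.

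Handedness is in none of the three.

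**The concern.** A variable is controlled in a group comparison if it is balanced by design or adjusted for in the model. In the three secondary imaging analyses handedness is neither. Yet regional cortical and subcortical measures, connectome node measures and task activation (with joystick responses, see MIST paradigm) can all differ between left and right hemispheres, which is the article's own reason for recording handedness.

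If the plan is followed as written, an imbalance in left-handers between groups of 30 passes into lateralised group differences in these analyses, while readers are told that handedness was controlled. The covariate lists are stated in the article itself, so this is not a detail left to a fuller document. A later analysis plan that added the EHI score would depart from the lists given here.

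**Working it through.** **1. Claim against model.**

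| Analysis | Matched on handedness | EHI in stated covariates |
|---|---|---|
| rsFC (Primary outcomes) | no | not in the firm list; to be *considered* |
| Structural MRI (Secondary outcomes) | no | no |
| DTI (Secondary outcomes) | no | no |
| Task-fMRI (Secondary outcomes) | no | no |

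**2. Where hemispheres are separated.** The primary rsFC analysis is described thus: "Six a priori fronto-limbic ROIs will be examined: bilateral amygdala, hippocampus, ACC, insula", followed by two prefrontal regions, with 15 pairwise connections. The count is k(k−1)/2. Six nodes give 6×5/2 = 15, the article's figure. Twelve nodes, with left and right separate, would give 12×11/2 = 66. So each bilateral region is one node, and the primary edges have no separate left and right nodes. By the article's own reasoning, handedness should matter least there. The exploratory seed-to-voxel rsFC analyses test voxels across the whole brain and so can be hemisphere-specific.

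**3. How likely an imbalance is.** The article says only that few left-handers are expected, so the rate p is an assumption. With independent Binomial(30, p) counts in the three groups:

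| Assumed p | Expected per group (30p) | P(a given pair differs by ≥ 3) | P(any pair differs by ≥ 3) |
|---|---|---|---|
| 8% | 2.4 | 0.226 | 0.440 |
| 10% | 3.0 | 0.275 | 0.515 |
| 12% | 3.6 | 0.315 | 0.570 |

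Over a wider range of 5% to 15%, the given-pair figure runs from 0.131 to 0.362 and the any-pair figure from 0.273 to 0.630.

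**4. Size of the bias.** A gap of three in 30 is 3/30 = 0.10. The shift in a group difference is 0.10 × (left-hander minus right-hander difference). For an assumed difference of 0.3 to 1.0 SD:
- 0.10 × 0.3 = 0.03 SD
- 0.10 × 1.0 = 0.10 SD

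**5. Effect on error rate.** For a two-group t-test with 30 per group (58 df), the noncentrality is shift × √(30/2). That is 0.03 × 3.873 = 0.116 and 0.10 × 3.873 = 0.387. The two-sided 5% error becomes about 5.1% and 6.7%, given that an imbalance of this size has occurred.

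**6. Cost of adjusting.** The article states no Cohen's f. N = 84, α = 0.05 and power 0.80 with three groups imply f ≈ 0.345. Using that f in a one-way F-test at N = 90, with no gain in explained variance:
- Structural, DTI and task models, from 3 to 4 covariates: residual df go from 90 − 3 − 3 = 84 to 83, and power from 0.8287 to 0.8286.
- rsFC model, from 5 to 6 covariate terms: power goes from 0.8284 to 0.8282.

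**The case against.** The best defence is that the Primary outcomes text is simply the working version of Table 1's shorthand: no matching, because left-handers are few, and handling by covariate instead. Much of this stands, and it rules out three stronger readings.

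- *A contradiction on matching.* There is none. Table 1 matches on sex and age only and lists handedness separately.
- *No control anywhere that hemispheres can differ.* The documents do not support this. The article speaks of rsFC analyses in the plural, which can cover the hemisphere-specific seed-to-voxel analyses.
- *EHI will be left out of the rsFC models.* The verb can mean either weighed as a possible covariate or treated as one. The text is ambiguous; it does not announce an omission.

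It is also fair to say that the three affected analyses are secondary, that the hormonal primary outcome has no hemisphere dimension, and that chance imbalance averages to no bias unless handedness is related to group or recruitment, for which the article gives no evidence. With about three left-handers per group, a linear term in a skewed score rests on few observations, so leaving it out of a secondary model is a defensible choice.

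None of this reconciles an unqualified claim of control with three explicit covariate lists that lack the variable. The same Table 1 sentence also covers school type and contraceptive intake, which no listed model contains either. That shows the wording is loose more generally; it does not excuse it here.

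**Conclusion.** The point holds as a minor mismatch between claim and model. Table 1 and the Strengths and limitations section claim more than the plan delivers: in the structural MRI, DTI and task-fMRI group comparisons, handedness is neither matched nor adjusted for. For rsFC the commitment is unclear rather than absent.

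The consequence is small. A shift of 0.03–0.10 SD compares with the d of about 0.4 to 1.3 cited in the sample size section, and it is unlikely to change a conclusion. The size rests on two assumptions that the documents do not supply: 8–12% left-handers and a left-right-hander difference of 0.3–1.0 SD. The mismatch itself rests on no assumption. The reason to act is that the statement can be made true, or made accurate, at almost no cost.

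**What to change.** Either of two changes resolves it.

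1. **Make the claim true.** Under Secondary outcomes, add the EHI score (already collected) as a covariate to the structural MRI, DTI and task-fMRI group models. Under Primary outcomes, replace *will be considered as covariates* with *will be included as a covariate*.
2. **Make the claim accurate.** Limit the handedness statements in Table 1 and in Strengths and limitations to the rsFC analyses, and still settle the verb under Primary outcomes.

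The first option costs one degree of freedom per model, and the planned N of 90 is unaffected. Its limit is that a linear term in a skewed score, with few left-handers, may adjust only partly, so the text should not promise full control. The second option changes wording only.
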